### Data analysis

An intention-to-treat analysis will be performed. Two-way repeated measures analysis of variance (ANOVA) will be used to evaluate the treatment effects among the three treatment groups at the three assessments from different time points. The between-subject factor will be the group and the within-subject factor will be the time. The treatment efficacy will also be examined by determining the number of participants whose change score reaches the minimal clinically important difference (MCID) in the clinical outcomes, by using a chi-square test. The MCID values will be adopted either for the established values of outcomes or 10% of the total scores when it has not been established. A *p* value < 0.05 will be considered as indicating statistical significance.

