## Methods/design

### Study design and procedure

This study protocol conforms to the Standard Protocol Items: Recommendations for Interventional Trials (SPIRIT) guidelines (see Additional file 1). This three-arm, single-blind, randomized controlled trial will investigate the treatment effects of AOT and MT versus a control intervention and accords with the SPIRIT Figure (Fig. 1). An estimated 90 patients with subacute stroke will be recruited to participate in this study. Each participant will receive 15 training sessions for 3 weeks. Licensed occupational therapists will be well trained in treatment protocols and study procedures to ensure the consistency of intervention delivery. The therapists were not blinded to the group assignment, given the nature of the intervention. In addition, all outcome measures will be administered to the patients by the same rater, who will be blinded to the subject’s group. Three evaluation time points will be used: baseline, immediately after 3 weeks of treatment, and 3 months after treatment. Prior to administration of outcome measures, a blinded rater will be trained on how to appropriately administer these assessments. Rater competence will be evaluated before proceeding to the trial.

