### Sample size calculation

To estimate the sample size, a-priori power analysis is performed on the data from previous AOT [8, 11] and MT literature [17, 24] in stroke rehabilitation. Based on the previous data of the treatment effects on motor function outcomes (e.g., FMA), an effect size (*d*) of 0.60 to 0.95 is expected which corresponds approximately to an effect size (*f*) of 0.30 to 0.50 for a study design of three-group comparisons. An estimate of sample size requirements for each group in a three-group study design, given a power of 0.80 and a two-sided type-I error of 0.05, will be in the range of 21 to 36 patients. We therefore plan to recruit 30 participants in each group (a total of 90) in this study.

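### The planned repeated-measures ANOVA delivers the stated intention-to-treat analysis only if every visit is complete or missing values are imputed first; a mixed model would use all observed visits

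*Protocol article*

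**What the plan says.** The Data analysis section opens with the principle and fixes the model in the next sentence: "An intention-to-treat analysis will be performed. Two-way repeated measures analysis of variance (ANOVA) will be used to evaluate the treatment effects". The comparison spans the three groups and all three assessments. The factors are given as follows: "The between-subject factor will be the group and the within-subject factor will be the time". The assessments are set under Study design and procedure: "Three evaluation time points will be used: baseline, immediately after 3 weeks of treatment, and 3 months after treatment".

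This ANOVA is the only model named for the continuous clinical outcomes, including the primary FMA score. The article names no mixed model and no imputation. It also does not say that patients with a missed visit will be excluded. The Objectives section asks for both the immediate and the retained effect. The Sample size calculation plans 30 patients per group and mentions no allowance for dropout.

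**The concern.** Classical two-way repeated-measures ANOVA works on complete rows: a patient contributes all three values or none. Intention-to-treat asks that every randomised patient be analysed as assigned. The two agree while every row is complete, or has been completed by imputation. Once a visit is missed and not imputed, they part.

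The practical weakness is that the last visit controls the earlier comparison. A patient assessed at 3 weeks but not at 3 months is removed from the immediate comparison too, although that value was observed. At stake are precision for the immediate effect and, under some dropout patterns, an unbiased estimate of it.

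**Working it through.** **Inputs from the article.** 90 patients, 30 per group; three assessments; power stated "given a power of 0.80 and a two-sided type-I error of 0.05"; effect size f from 0.30 to 0.50. The article gives no dropout rate, so there is no figure of its own to reproduce on this point.

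**Assumptions (not in the article).** 10–20% of patients miss the 3-month visit. For the bias illustration: FMA SD 11.5; correlations 0.8 (baseline with post-treatment), 0.7 (baseline with 3 months) and 0.85 (post-treatment with 3 months); true post-treatment difference 5 points between two arms, measured as change from baseline.

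**1. Patients removed.** 0.10 × 90 = 9 and 0.20 × 90 = 18. If 5% miss the post-treatment visit and 20% the 3-month visit, and everyone missing the first also misses the second, then 80% remain and 20% − 5% = 15% of patients lose a post-treatment value that was observed. If the misses are independent, 0.95 × 0.80 = 76% remain.

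**2. Precision of the immediate comparison.** The standard error scales with 1/√n.
- 10% loss: n = 27 per group, √(30/27) = 1.05
- 20% loss: n = 24 per group, √(30/24) = 1.12

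As a guide to power, take a one-way three-group F test with noncentrality λ = f²N. At f = 0.30 it needs 37 per group for 80% power, close to the stated upper figure of 36, so f = 0.30 is a fair reference.

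| Loss | n per group | λ = 0.09 × 3n | Power |
|---|---|---|---|
| 0% | 30 | 8.10 | 0.71 |
| 10% | 27 | 7.29 | 0.66 |
| 20% | 24 | 6.48 | 0.60 |

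**3. Bias of the immediate comparison among completers** (large-sample simulation, true difference 5.0).

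| Who misses the 3-month visit | Completers' difference |
|---|---|
| Random, or dependent on gain equally in both arms at equal rates, 10–20% | 5.0–5.1 |
| Poor gainers in control, random in active arm, weaker dependence, 10 / 15 / 20% | 4.5 / 4.3 / 4.1 |
| The same, stronger dependence, 10 / 15 / 20% | 4.1 / 3.6 / 3.2 |

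A second run of the one-arm pattern, with a logistic dropout rule at 15% loss, gave 4.2–4.6. The shortfall in the one-arm pattern therefore runs from 5.0 − 4.6 = 0.4 to 5.0 − 3.2 = 1.8 points.

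An upper limit can be checked by hand. The SD of change is 11.5 × √(2 − 2 × 0.8) = 7.27. If exactly the lowest fraction p of gainers left control, its mean change would rise by 7.27 × φ(z_p)/(1 − p), where φ is the standard normal density at the p quantile. This is 1.4, 2.0 and 2.5 points at p = 0.10, 0.15 and 0.20. The simulated shortfalls lie below these limits, as they should.

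A separate simulation (SD 10, true difference 4.0) agrees in pattern. The same rule on gain in both arms gave 3.8. A rule running in opposite directions in the two arms, with 20% and 27% missing, gave 2.3.

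**4. What a likelihood-based model does.** In the one-arm illustrations it returns 5.0 at post-treatment. That is by construction: loss there depends only on values already observed, and the model uses them.

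**The case against.** The strongest reply is that the article never says incomplete patients will be deleted. Intention-to-treat followed by ANOVA on an imputed data set is coherent and fits the wording. A condensed article may leave its missing-data rule to the full protocol or the SAP, so its absence is not a fault. This stands. A reader might infer that the analysis simply becomes a completers' analysis, or that the two sentences flatly contradict each other. The text supports neither without two conditions: visits are missed, and values are not imputed beforehand.

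A reader might also infer that the treatment effect will be biased by a point or more. The article gives no dropout rate or mechanism. All arms receive dose-matched, therapist-delivered training on the same task categories, and the rater is blinded. Patients can tell whether they have a video, a mirror or neither, so loss that differs by arm is possible, but nothing in the text makes it the expected case.

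Finally, a reader might add that the test ignores sphericity. The Data analysis section does not say that the test will be uncorrected, and a correction is ordinary SAP detail. Even uncorrected, 20,000 null simulations at 30 per group rejected in only 5.5–5.9% of runs. That is no part of this point.

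What the reply does not remove is that the named model cannot by itself keep a patient with one missing visit, and that a standard alternative can.

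**Conclusion.** The concern holds in conditional form. As worded, the ANOVA delivers intention-to-treat only with complete or imputed data. If visits are missed and not imputed, loss of precision in the immediate comparison is certain: about 5–12% on the standard error for an assumed 10–20% loss, from a plan with no stated dropout allowance. Bias may be nil or may exceed a point, depending on a mechanism the documents do not give; the figures of 0.4 to 1.8 points belong to the one-arm pattern only. It is a worthwhile improvement to the primary analysis rather than a defect that invalidates the plan.

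**What to change.** For the FMA and the other continuous outcomes, replace the ANOVA with a likelihood-based linear mixed model for repeated measures: group, visit and group-by-visit, unstructured covariance, all randomised patients as assigned, every observed visit used. This restores the observed post-treatment values in full. For the 3-month comparison it recovers only what earlier visits predict, and it relies on loss being explained by observed data.

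Alternatively, keep the ANOVA and apply it after multiple imputation specified in advance.

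The cost is revised analysis wording and a standard software procedure, with no new data. The Trial status section says recruitment was ongoing at submission, so the change could be made at that stage, before any unblinded analysis.

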## Background

Stroke is the leading cause of long-term adult disability worldwide [1]. Most patients with stroke experience upper-extremity (UE) motor impairment [2] and show minimal recovery of the affected arm even 6 months after stroke [3]. Due to the potentially severe adverse effects after stroke, it is critical in clinical practice to develop effective and specific stroke interventions to improve arm function and to explore the neural mechanisms involved [4, 5]. Action observation therapy (AOT) and mirror therapy (MT) are two examples of novel approaches concerning stroke motor recovery that are supported by neuroscientific foundations [6, 7]. However, the relative efficacy of AOT versus MT has not been validated in patients with stroke.

AOT is a promising approach grounded in basic neuroscience and the recent discovery of the mirror neuron system (MNS) [6]. AOT commonly includes action observation and action execution and allows patients to safely practice movements and motor tasks. AOT is recommended to help patients with stroke to form accurate images of motor actions [8] and to mediate their motor relearning process after stroke [6]. Researchers have found that AOT can induce stronger cognitive activity than motor imagery in patients with stroke and have suggested that AOT could be an effective approach for patients who have difficulty with motor representation [9]. AOT is a new approach in stroke rehabilitation; therefore, only a few studies have targeted enhancement of UE motor recovery and investigated the effects of AOT in patients with stroke [8, 10–14]. Based on these studies, AOT has been shown to be a beneficial and effective approach to improve patient motor function. However, the heterogeneity of study designs and small sample sizes of the studies lead to no clear conclusions about the efficacy of AOT in stroke rehabilitation.

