### Objectives

The main purposes of this clinical trial are to (1) compare the immediate and retention treatment effects of AOT and MT on different outcomes with those of a dose-matched control group and (2) explore and compare the neural mechanisms and changes in cortical neural activity associated with the effects of AOT and MT in stroke patients, using magnetoencephalography (MEG).

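### The analysis section names no deciding effect, time point or contrast for the primary FMA outcome, so it cannot show which therapy beat control, and counting any of its named tests as success raises the false-positive rate to about two to three times 5%

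*Protocol article*

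**What the plan says.** All references are to the protocol article.

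- **Objectives.** The first aim is to "compare the immediate and retention treatment effects of AOT and MT on different outcomes with those of a dose-matched control group". That is two contrasts with control at two follow-up visits.
- **Background.** It remarks that "the relative efficacy of AOT versus MT has not been validated in patients with stroke". For clinical outcomes this is motivation. The Objectives plainly compare AOT with MT only for neural mechanisms.
- **Outcome measures.** FMA is primary, measured at baseline, after 3 weeks of treatment and 3 months after treatment. No visit is named as primary.
- **Data analysis.** A repeated measures ANOVA with group between subjects and time within subjects "will be used to evaluate the treatment effects among the three treatment groups at the three assessments from different time points". Efficacy is also to be examined by a chi-square test on the number of patients whose change reaches the MCID, with no visit given. For all of this, a p "value < 0.05 will be considered as indicating statistical significance".
- **Sample size calculation.** The trial is sized "given a power of 0.80 and a two-sided type-I error of 0.05", with an effect size f "of 0.30 to 0.50 for a study design of three-group comparisons", so for an omnibus comparison rather than a pairwise one.

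**The concern.** The objective asks whether each therapy does better than control, and separates the immediate from the lasting effect. The named tests ask only whether the three groups differ somewhere. A significant group-by-time interaction would fit AOT working, MT working, both working, or one doing worse than control, at either follow-up.

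The section also leaves open what counts as a positive FMA result. The ANOVA yields a group effect and an interaction, and the chi-square test can be run at either or both follow-ups. All share the same unadjusted threshold and none is ranked above another. At stake are the ability to name the effective therapy and the 5% error rate on the primary outcome.

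**Working it through.** **1. The plan's own figure.** For a one-way three-group F test at alpha 0.05 and power 0.80, f = 0.30 needs 37 per group, close to the stated upper figure of 36. For f = 0.50 the same formula gives 14, not the stated lower figure of 21. That mismatch is a separate matter. What counts here is that the sizing is for a three-group test: with 30 per group its power is 71% at f = 0.30.

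**2. What the named effects measure.** The interaction has (3 − 1) × (3 − 1) = 4 numerator degrees of freedom and points to no single contrast or visit. The group effect averages all three visits, including baseline. If a therapy adds δ at both follow-ups, the averaged difference is (0 + δ + δ)/3 = 2δ/3. If it adds δ only after treatment, the averaged difference is δ/3. The group effect therefore dilutes the treatment effect, yet nothing in the section excludes it.

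**3. False-positive rate of the named tests.** For two independent tests at 0.05, the chance of at least one false positive is 1 − 0.95² = 9.75%. The actual tests are correlated, so they were simulated with no difference between groups, using 20,000 trials per setting.

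- From the documents: three groups, 30 per group, three visits, alpha 0.05.
- Assumed: SD 10; equal correlation between visits of 0.5 to 0.9; common gains of 5 and 6 points at the two follow-ups; responder threshold 6.6 points (10% of 66), with 5 points as a variant; no dropout.

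| Results that would count as success on FMA | At least one p < 0.05 | Multiple of 5% |
|---|---|---|
| One ANOVA effect alone | about 5% | 1 |
| Interaction, or chi-square at one follow-up | 8.4 to 8.9% | 1.7 to 1.8 |
| Group effect or interaction | 9.5 to 10.0% | 1.9 to 2.0 |
| Interaction, or chi-square at either follow-up | 11.6 to 12.0% | 2.3 to 2.4 |
| Group effect, interaction, or either chi-square | 15.8 to 16.5% | 3.2 to 3.3 |

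A separate run with SD 11.5, unequal correlations (0.7 to 0.85) and gains of 6 and 8 gave 10% for the interaction or either chi-square, and 15% with the group effect added.

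**4. Does gating hold 5%?** Take three groups at one visit, with pairwise tests made only after a significant F test.

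- If all three means are equal, a false claim needs a false-positive F test: at most 5%.
- If exactly one pair is equal, only that pair can be falsely claimed, and it is tested at 5%. Simulation gave 4.7 to 5.1%.
- If no pair is equal, no false claim of a difference is possible.

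**5. Cost of splitting alpha instead.** Pairwise power is approximately Φ(d√(n/2) − z), where z is the two-sided critical value. With n = 30 and d = 0.60, the lower end of the plan's range, d√(n/2) = 0.60 × √15 = 2.32. At alpha 0.05 this gives Φ(2.32 − 1.96) = 64%; at 0.05/3 = 0.0167, Φ(2.32 − 2.39) = 47%. The gate avoids that loss from a smaller alpha, although each pairwise claim then also needs a significant F test.

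**The case against.** This is a condensed article with no analysis plan shown, and contrasts and multiplicity rules after an ANOVA are commonly left to such a plan. Their absence alone is therefore no finding. The responder analysis reads naturally as supplementary, the interaction is the natural test of differential change, and 0.05 may be only a generic threshold. On that reading the interaction alone decides, and its error rate is about 5%. This stands to the extent that the inflated rates are conditional on how success is declared. It does not remove the point: the section itself names two kinds of efficacy test, gives both one threshold, and leaves the deciding effect and visit open.

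Three stronger readings are tempting but unsupported.

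- **That the error rate quadruples.** About 21 to 22% arises only if three pairwise contrasts are tested at both follow-ups without a gate. The article plans no such tests.
- **That 5% is lost however the trial proceeds.** The interaction alone holds it. Pairwise tests after a significant interaction gave 4.6 to 4.8% over both visits when no groups differ. Control over both visits when one arm differs was not checked.
- **That AOT versus MT on clinical outcomes is a stated objective left untested.** It appears in the Background; the clinical objective is framed against control.

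It can also be said that baseline adjustment and a 3-week primary visit are preferences. The visit is indeed the investigators' choice, provided that one is fixed in advance.

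**Conclusion.** The point holds in limited form. As written, the analysis cannot show which therapy differs from control, which is the first objective, and it does not fix what decides the primary outcome. That part rests on the text alone and needs no assumption.

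The numerical part is conditional. If any one named test counts as success, the FMA false-positive rate is about two to three times the nominal 5%: roughly 9 to 12% for the interaction with one or two chi-square tests, and about 16% with the group effect added. The SD, correlations, gains and 6.6-point threshold are not in the article for this purpose; the 10% rule applies only where no MCID is established, and the article does not say whether that covers FMA. Across the settings tried, including a 5-point threshold, the rates moved little. The article does not show that any inflated claim will be made, only that its wording permits one.

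**What to change.** Name one primary test: a three-group F test at 0.05 on FMA adjusted for baseline FMA, at one pre-stated visit, for example the end of the 3-week treatment. Only if it is significant, test AOT–control, MT–control and AOT–MT each at 0.05, without splitting alpha. State that the ANOVA group effect is not an efficacy test. Keep 3-month FMA as key secondary for retention. Report the MCID responder tests and other outcomes as supportive, with confidence intervals.

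This matches the three-group sizing and needs no more patients or assessments. In two simulated settings with an assumed treatment effect, the baseline-adjusted test had about 82% power against 74% for the interaction, and 55% against 47%. The gain depends on the assumed correlation between visits, and the recommendation does not rest on it.

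The cost is wording, to be settled before results are known; the article reports recruitment as ongoing at submission. The downside is that the retention and responder tests lose primary confirmatory status and the pairwise tests depend on the omnibus gate.

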### Patient inclusion and exclusion criteria

The inclusion criteria of the participants will be: (1) diagnosed as having a unilateral stroke, (2) 1 to 6 months after stroke onset, (3) from 20 to 80 years of age, (4) a baseline score of the Fugl-Meyer Assessment (FMA) of 20 to 60 [28], (5) able to follow the study instructions (measured by the Taiwan version of the Montreal Cognitive Assessment) [29], and (6) capable of participating in therapy and assessment sessions. The exclusion criteria will be: (1) global or receptive aphasia, (2) severe neglect, and (3) major medical problems or comorbidities that influenced UE usage or cause severe pain.

In addition, if patients have no metal implants, no head traumas or neurosurgical operations, and can perform MEG motor tasks, they can additionally participate in the MEG assessment. For the MEG portion of the study, we expect to recruit 12 to 15 patients in each group. Patients can still participate in the study, receiving rehabilitation therapy and clinical evaluations, even if they do not meet the MEG eligibility criteria, or are not willing to participate in the MEG study. All participants must provide written informed consent before entering the study.

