### Randomization

The participants will be randomly allocated to one of the three treatment groups in a 1:1:1 ratio after baseline evaluation. The participants will be pre-stratified on the basis of the severity of UE motor deficits (FMA score: 20 to 40 (moderate-to-severe) versus 40 to 60 (mild-to-moderate) [28]) and side of lesion (right versus left) to assure baseline equivalence between the groups. The random assignments will be performed online using a web-based randomization tool (freely available at https://www.randomizer.org/). A research assistant who will not be involved in outcomes assessment or screening of subjects will independently manage the randomization procedure according to allocation concealment.

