### Outcome measures

Clinical outcome measurements will be administered to the participants at baseline, immediately after 3 weeks of treatment, and 3 months after treatment. The primary outcome will be the FMA score. Secondary outcomes will include the modified Rankin Scale (mRS), the Box and Block Test (BBT), the ABILHAND questionnaire, the Questionnaire Upon Mental Imagery (QMI), the Functional Independence Measure (FIM), activity monitors, and the Stroke Impact Scale (SIS) version 3.0.

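### The repeated measures ANOVA uses the pre-randomisation FMA as a third outcome level, so the treatment comparison rests on raw change and gives up precision and protection against baseline imbalance.

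*Protocol article*

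**What the plan says.** The Outcome measures section of the protocol article states: "The primary outcome will be the FMA score". The Data analysis section names the model, a two-way repeated measures ANOVA, and what it is to assess: "treatment effects among the three treatment groups at the three assessments from different time points". It then fixes the factors: "The between-subject factor will be the group and the within-subject factor will be the time". No covariate is named.

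The Study design and procedure section defines the assessments: "Three evaluation time points will be used: baseline, immediately after 3 weeks of treatment, and 3 months after treatment". Under Randomization, patients are "randomly allocated to one of the three treatment groups in a 1:1:1 ratio after baseline evaluation". The same section adds: "The participants will be pre-stratified on the basis of the severity of UE motor deficits", with FMA bands 20 to 40 and 40 to 60, and with side of lesion as the second stratification factor. Neither the band nor the baseline score appears in the analysis model.

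Entry requires "a baseline score of the Fugl-Meyer Assessment (FMA) of 20 to 60", on a scale that runs from 0 to 66.

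**The concern.** Baseline FMA is measured before allocation, so it is not an outcome of treatment. Placed among the outcome levels, it turns the group-by-time contrasts against baseline into differences in raw change (follow-up minus baseline). That is the same as assuming that follow-up FMA rises by exactly one point for each point of baseline FMA.

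The trial's own limits cast doubt on that assumption. A patient who enters at 60 can gain at most 66 − 60 = 6 points. A patient who enters at 20 can gain 66 − 20 = 46.

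If the true slope is below 1, two things follow. The primary comparison is less precise than the collected data allow. In addition, a chance difference in baseline FMA between arms passes partly into the estimated effect. Precision matters here because the planned 30 per group lies below the upper end (36) of the article's own stated requirement.

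**Working it through.** **Inputs from the article.** Three arms, 30 per arm; baseline FMA 20 to 60, stratified at 40; two post-randomisation assessments; two-sided alpha 0.05; effect size f = 0.30 to 0.50.

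**Inputs not in the article, assumed over a range.** Correlation r between baseline and follow-up FMA; slope of follow-up on baseline; residual SD; correlation of the two follow-up residuals; uniform baseline distribution.

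**Step 1: the article's figure.** For a three-group F test, λ = N·f². With f = 0.30 and 80% power this needs 37 per group (the article says 36). At 30 per group, λ = 90 × 0.09 = 8.1 and power is 70.7%. The other end does not reproduce: f = 0.50 needs 14 per group, not 21. That is a separate matter and is not used below.

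**Step 2: equal-variance comparison.** With common variance σ² at baseline and follow-up:

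- change score: variance 2σ²(1 − r)
- baseline-adjusted score: variance σ²(1 − r²)
- ratio, adjusted to change: (1 + r)/2

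Taking f = 0.30 on the change scale, where the unadjusted power is 70.7% and the requirement is 37 per group:

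| r | Variance ratio | Adjusted power, 30 per arm | n per arm for 80% |
|---|---|---|---|
| 0.5 | 0.75 | 83.2% | 28 |
| 0.7 | 0.85 | 78.0% | 32 |
| 0.8 | 0.90 | 75.5% | 34 |
| 0.9 | 0.95 | 73.1% | 35 |

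**Step 3: the FMA entry range.** Take baseline uniform on 20 to 60, so its variance is 40²/12 = 133.3. Take residual SD 5 and residual correlation 0.7 between the two follow-ups. The residual variance of their mean is 25 × (1 + 0.7)/2 = 21.25, which is the adjusted variance. The change-score variance is (1 − slope)² × 133.3 + 21.25:

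| Slope | Change-score variance | Adjusted / change |
|---|---|---|
| 0.9 | 1.33 + 21.25 = 22.58 | 0.94 |
| 0.8 | 5.33 + 21.25 = 26.58 | 0.80 |
| 0.7 | 12.00 + 21.25 = 33.25 | 0.64 |

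These ratios differ from step 2 because follow-up variance is now smaller than baseline variance: follow-up SD is about 10.5 and 9.5 at slopes 0.8 and 0.7, against 11.5 at baseline. The corresponding correlations are 0.88 and 0.85. The two steps are different scenarios and should not be read as one.

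**Step 4: power under step 3, by simulation.** Stratified allocation, both therapies 3 points better than control at both follow-ups. The last two columns are both 2-df tests on the mean of the two follow-ups, so they compare like with like.

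| Slope | Group-by-time F (4 df) | Raw change (2 df) | Baseline-adjusted (2 df) |
|---|---|---|---|
| 0.9 | 69–71% | 69–71% | 71–74% |
| 0.8 | 62–64% | 62–63% | 72–75% |
| 0.7 | 54–55% | 49–51% | 72–74% |

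Ranges are across independent simulations. Apart from simulation error, the adjusted power does not depend on the slope and is about 73%. With residual correlation 0.5 the three tests give 66/76/78%, 61/67/79% and 50/52/78% at slopes 0.9, 0.8 and 0.7. With residual SD 7 and slope 0.8, the planned test has 37% and the adjusted test 43%. With no treatment effect and slope 0.7, the planned test rejects only about 2% of the time: the design balances the FMA band, but the analysis leaves band variance in the error term.

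**Step 5: chance imbalance.** Within a band the baseline variance is 20²/12 = 33.3. The standard error of a between-arm baseline difference is √33.3 × √(2/30) = 1.49 points (about 3.0 without stratification). Raw change passes (1 − slope) of the difference, with opposite sign, into the estimate. A one-SE imbalance shifts it by 0.3 points at slope 0.8 and 0.45 at slope 0.7. A 3-point imbalance, about two standard errors, shifts it by 0.6 to 0.9.

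**Step 6: the other reading of the model.** The article does not say which ANOVA term tests treatment. If it were the group main effect, the untreated baseline level would dilute the effect. With a 0.6 SD effect, simulated power for the main effect is 48% at r = 0.5 and 41% at r = 0.7. Group-by-time has 68% and 90%, and baseline adjustment 92% and 98%.

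**The case against.** Repeated measures ANOVA with group and time is a standard analysis. It is unbiased over randomisations and does not inflate type I error. Covariates are often left to an analysis plan, which is not shown here. This stands in part: the point is about efficiency, not validity. It is not an omission, however, because the article itself states the model, its factors and its levels.

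The size is uncertain, and that stands too. The documents give no slope, SD or correlation. Gains of 6 and 46 points are bounds, not expected gains, so they make a slope of 1 doubtful but do not establish another value. A hard ceiling is also non-linear, and a linear covariate corrects it only in part. At slope 0.9 or r = 0.9 the gain is about 2 percentage points of power. A 3-point imbalance is a tail case.

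Two technical objections have force. First, adding only the FMA band would recover much of the gain: at slope 0.7 the change-score variance falls from 33.25 to 0.09 × 33.3 + 21.25 = 24.25, against 21.25 with the full score, which is 9/12 or three quarters of the reduction. But the stated model does not include the band either. Second, a joint 4-df baseline-adjusted test over both visits had 62%, 61% and 59% power against 70%, 63% and 54% for the planned F test, so it gains only at slope 0.7. The benefit comes from estimating the group differences directly, not from replacing one omnibus test by another.

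**Conclusion.** The concern holds. The stated model places a pre-randomisation measurement on the outcome side and uses neither the baseline score nor the stratification band for adjustment. On the natural reading, group-by-time, the FMA effect rests on raw change.

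The direction is certain whenever the slope differs from 1; the size is not. In like-for-like 2-df tests the loss is about 2 to 3 percentage points of power at slope 0.9, about 10 to 12 at 0.8 and more than 20 at 0.7, assuming residual SD 5, a 3-point effect and a uniform baseline. Under equal variances and f = 0.30 it is 2.4 points at r = 0.9, 4.8 at r = 0.8, 7.3 at r = 0.7 and 12.5 at r = 0.5. The planned test remains valid, so this is a change the sponsor should make rather than an error that invalidates the trial.

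**What to change.** In the Data analysis section, make the 3-week and 3-month FMA scores the outcomes and move baseline FMA to the covariate side. The model terms are group, visit, group-by-visit, baseline FMA and baseline-by-visit. State that the treatment effects are the group differences at 3 weeks and at 3 months estimated from this model, not a single joint test over both visits. These match the immediate and retention effects in the Objectives. Adding the stratification factors would be consistent with the design. Treat each other clinical outcome in the same way, with its own baseline value.

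The cost is a change of wording and one or two degrees of freedom for the baseline terms, plus one for each stratification factor if added. No new data or patients are needed. The article reports recruitment as ongoing at submission, so on that status the change could be made before the analysis.
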